**Methods:**

A total of 70 healthy, physically inactive (<150 minutes/week of physical activity) adults (aged 18-45 years) will be randomly assigned to an intervention or control group. Participants in the intervention group will receive weekly training using progressive endurance and interval running adapted individually to their remotely supervised home training performance via web-based coach support. A standardized incremental treadmill exercise test will be performed before and after the intervention period of 8 weeks to determine the innate and acquired aerobic capacity (peak oxygen uptake). Before and after the intervention, psychological tests and questionnaires that characterize parameters implicated in resilience will be applied. Blood and saliva will be sampled for the analysis of cortisol, lactate, endocannabinoids, catecholamines, kynurenic acid, and further circulating signal transducers. Statistical analysis will provide comprehensive knowledge on the relationship between aerobic capacity and resilience, as well as the capacity of peripheral factors to mediate the promoting effects of exercise on resilience.

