### Randomization

The included participants will be randomly assigned with a 50%-50% allocation to the IG or CG. Randomization will be performed using the EXCEPT NUMBER command in Microsoft Excel. In addition, randomization will be stratified by gender with an expected ratio of 50%-50% and BMI with an expected ratio of 33% overweight (BMI ≥25) and 67% normal weight (BMI <25) to recruit CG and IG participants with homogeneous baseline characteristics.

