### Statistical Methods

The power calculation was based on the analyses of the primary outcomes, that is, aerobic capacity (VO_2_peak) and experimental stress reactivity (saliva cortisol). On the basis of the results of Bacon et al [122], the sample size was determined a priori via power analysis (G*Power V5), yielding a minimum sample size of 67 for a medium-to-large effect size of *f(V)*=0.35. An alpha error set to .05 and statistical power of 0.80 were assumed for a multivariate analysis of variance (MANOVA) with 2 repeated measurements, 2 groups, and interaction effects. Descriptive statistics will be used for all outcome measures at each time point to give an overview of all results. First, MANOVA will be performed with the main primary outcomes as dependent variables, that is, aerobic capacity (VO_2_peak) and experimental stress reactivity (saliva cortisol) to maximize the power of the analyses and to be able to investigate the main and interaction effects of time (baseline [T0, T1] vs post [T2, T3]) and group (IG vs CG). Groups should be equal at preintervention (T0 and T1). A time effect should be observed for the IG. Furthermore, we expect a significant time×group interaction as the IG should react differently over time, with a higher increase in aerobic capacity (VO_2_peak). Significant effects of the MANOVA will be followed up by posthoc analyses of variance. As a secondary aim of our study, we aim to identify variables (eg, emotion regulation and biological metrics) that mediate the relationship between physical exercise and resilience outcomes. To that end, we plan to calculate multiple regression analyses that include potential mediators. Principal component analyses regarding potential mediating variables will precede the mediator analyses to avoid redundancy in our regression models. This will be statistically detailed with posthoc tests and corrections for multiple comparisons (Bonferroni-Holm correction [123]). Missing data will be omitted from the data set.

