## Results

The study was registered in October 2019 (DRKS00018078). Enrollment began in September 2019 and was paused from April 2020 until submission of this study protocol because of the COVID-19 pandemic. Of the 161 interested people who have contacted us so far, 26.7% (43/161) fulfilled the inclusion criteria. Among the 55% (17/31) participants in the IG and 45% (14/31) participants in the CG, who completed the study (N=31), no serious adverse incidents were reported. Within the program, 9% (4/43) of participants (2/17, 12% in the IG and 2/14, 14% in the CG) withdrew because of individual reasons (dropout rate 11.4%). Approximately 19% (8/43) have not yet participated in the program because of the COVID-19 pandemic. Although the COVID-19 pandemic does not affect the web-based exercise training approach, the study had to be paused in April 2020, as it was not possible to determine the primary and secondary end points (VO_2_peak and cortisol levels) because of the lockdown of the laboratory facilities. Further study recruitment will resume when COVID-19 restrictions are completely lifted. On the basis of the experiences from the first recruitment period, the study is expected to continue for another 6 months to complete the intended sample size.

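### Omitting missing data, with 70 randomised against a minimum of 67, leaves about 62 analysable at the trial's own 11.4% dropout and restricts the primary comparison to completers

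*Protocol article*

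**What the plan says.** Statistical Methods gives the size as "yielding a minimum sample size of 67 for a medium-to-large effect size of *f(V)*=0.35". The settings are "An alpha error set to .05 and statistical power of 0.80 were assumed", for a MANOVA "with 2 repeated measurements, 2 groups, and interaction effects". The dependent variables of the primary MANOVA are VO2peak and salivary cortisol, each before and after the intervention. The section ends with the missing-data rule: "Missing data will be omitted from the data set".

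The number to be randomised is in the Abstract, Methods: "A total of 70 healthy, physically inactive (<150 minutes/week of physical activity) adults (aged 18-45 years) will be randomly assigned". The trial registration data set also gives 70 as the target. Randomization says participants are "randomly assigned with a 50%-50% allocation to the IG or CG". The article states no allowance for dropout.

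Results reports progress up to the pandemic pause: 43 people included, 31 completers (17 intervention, 14 control), 4 withdrawals and 8 not yet started. It gives the withdrawals by arm as "2/17, 12% in the IG and 2/14, 14% in the CG) withdrew because of individual reasons (dropout rate 11.4" percent.

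**The concern.** Three statements do not fit together: a minimum of 67, a target of 70, and a rule that removes whatever is missing. With that rule the number that counts for power is the number with complete data, and the article's own experience suggests a loss well above the three people the target allows for.

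The rule also matters for validity. The four primary values come from four visits: cortisol from the stress tests at T0 and T2, VO2peak from the treadmill tests at T1 and T3. A MANOVA on all four needs a complete set. Someone who attends T2 but misses T3 loses a measured cortisol response as well as the VO2peak that was never obtained. The comparison is then between those who finished in each arm, not between the arms as randomised. Strengths and Limitations itself names inexperience, fear, injury risk and reduced adherence as concerns with remote running training, so loss related to fitness or stress is plausible.

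Finally, the arm dropout rates look wrong on their face: a pooled 11.4% cannot lie below both arm rates of 12% and 14%.

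**Working it through.** **Inputs.** Effect size f(V) = 0.35, alpha 0.05, power 0.80, 2 groups, 2 measurements, minimum 67 (Statistical Methods). Number randomised 70 (Abstract, Methods). Completers 17 + 14 = 31, withdrawals 4, not yet started 8 (Results).

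**Step 1: reproduce the protocol's figure.** For the group-by-time interaction with one numerator degree of freedom, use the noncentral F with df1 = (2−1)(2−1) = 1, df2 = N − 2 and λ = N × 0.35² = 0.1225 N.

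| N | λ | Power |
|---|---|---|
| 62 | 7.595 | 0.774 |
| 63 | 7.718 | 0.781 |
| 66 | 8.085 | 0.7997 |
| 67 | 8.208 | 0.806 |
| 70 | 8.575 | 0.823 |

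The smallest N with power of at least 0.80 is 67, which matches the protocol exactly.

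**Step 2: tolerable loss.** (70 − 67)/70 = 3/70 = 4.3%.

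**Step 3: observed loss.** Starters are 31 + 4 = 35, and 35 + 8 = 43 accounts for everyone included. 4/35 = 11.4%, which is the printed overall rate. The exact 95% interval is 3.2% to 26.7%.

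**Step 4: expected complete cases.**
- At 11.4%: 70 × 31/35 = 62.0, power 0.774.
- At 4/43 = 9.3%: 70 × (1 − 0.093) = 63.5, so about 63, power 0.781.
- At the interval limits: 70 × 0.968 = 67.8 and 70 × 0.733 = 51.3.
- If the true rate is 11.4%, the binomial chance of keeping at least 67 of 70 is about 3%.
- The four withdrawals already exceed the margin of three. If all four lack post-intervention values and the number randomised stays at 70, at most 66 complete cases are possible.
- Keeping 67 complete at 11.4% would take 67/(31/35) = 75.6, so 76 randomised (74 at 9.3%).

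**Step 5: arm rates.** The printed denominators, 17 and 14, are the completers, so the people who withdrew are not in them. Starters by arm are 17 + 2 = 19 and 14 + 2 = 16.
- Intervention: 2/19 = 10.5% (printed as 2/17, 12%).
- Control: 2/16 = 12.5% (printed as 2/14, 14%).
- Pooled: 4/35 = 11.4%, which now lies between the two arms as it must.

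**The case against.** The sample size was set before any dropout was seen, and 11.4% rests on four events. The tolerable 4.3% lies inside the interval, so the shortfall is a projection and not an established result. That stands. The projected loss on the protocol's own calculation is also modest: about 3 points below 0.80.

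The rule speaks of omitting data, not people. The follow-up ANOVAs are run per outcome, so a missed treadmill test need not remove cortisol there. That also stands, but it does not help the MANOVA, which comes first and decides whether the ANOVAs are run.

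Analysis sets and sensitivity analyses are often left to a full protocol or SAP, and their absence here is no fault. The omission rule is different, because the article states it outright.

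Three stronger readings are tempting, and the document does not support them:
- **That dropout has biased the comparison.** Results reports two withdrawals in each arm, for individual reasons, and the controls received no training. Differential loss is not shown, though four events cannot exclude it. The data management section commits to reporting all dropouts and their reasons.
- **That dropout costs far more power because the MANOVA has two outcomes.** With the same f(V), two-outcome power is already 0.708 at 67 with nobody lost, so most of that gap is a separate sizing question. The protocol also does not say that the same effect size applies to a joint test.
- **That the arm-rate error affects the analysis.** It is a slip in a progress report. The pooled rate is right and no planned analysis uses the arm rates.

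**Conclusion.** The point holds in moderate form. At the trial's own dropout rate, 70 randomised with omission gives about 62 complete cases, five short of the stated minimum, and power of about 0.77. This assumes that 70 is the number randomised, as the Abstract says, and that those who withdraw lack post-intervention values. If recruitment were meant to continue until 70 people had completed, the shortfall would disappear, but the article does not say so.

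The more durable part is the rule itself. As written, it throws away measured primary-outcome values and confines the main comparison to completers. The direction and size of any resulting bias are unknown. This should be corrected before analysis, but it does not invalidate the design.

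**What to change.** 1. **Restate the expected size and power.** Say that at 11.4% dropout about 62 of 70 are expected to be analysable, with power of about 77% on the stated calculation, and note how imprecise the rate is.
2. **Replace the omission rule.** Analyse all randomised participants in their assigned arm, using every available primary-outcome value. One workable form is a likelihood-based mixed model for VO2peak at T1 and T3, and a baseline-adjusted analysis of T2 cortisol with multiple imputation. Adjustment fits the protocol's own statement, in Strengths and Limitations, that the two stress tests are not directly comparable. Keep the planned multiplicity control: the Bonferroni-Holm correction the protocol already names can cover the two endpoints. Report the complete-case MANOVA as a sensitivity analysis.
3. **Correct the arm dropout rates** in Results to 2/19 (10.5%) and 2/16 (12.5%).

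The cost is revised wording in Statistical Methods and Results, modest extra analysis work, and a slightly less favourable power statement. Because item 2 changes the lead analysis, it should be documented before outcomes are compared by arm. It mainly reduces bias and data loss: people with baseline values only add little information on change, so little power comes back. Restoring 67 complete cases would need about 76 randomised, which is a resource decision for the sponsor while recruitment is unfinished.

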## Results

The study was registered in October 2019 (DRKS00018078). Enrollment began in September 2019 and was paused from April 2020 until submission of this study protocol because of the COVID-19 pandemic. Of the 161 interested people who have contacted us so far, 26.7% (43/161) fulfilled the inclusion criteria. Among the 55% (17/31) participants in the IG and 45% (14/31) participants in the CG, who completed the study (N=31), no serious adverse incidents were reported. Within the program, 9% (4/43) of participants (2/17, 12% in the IG and 2/14, 14% in the CG) withdrew because of individual reasons (dropout rate 11.4%). Approximately 19% (8/43) have not yet participated in the program because of the COVID-19 pandemic. Although the COVID-19 pandemic does not affect the web-based exercise training approach, the study had to be paused in April 2020, as it was not possible to determine the primary and secondary end points (VO_2_peak and cortisol levels) because of the lockdown of the laboratory facilities. Further study recruitment will resume when COVID-19 restrictions are completely lifted. On the basis of the experiences from the first recruitment period, the study is expected to continue for another 6 months to complete the intended sample size.

## Discussion

### Benefits of the Study

Evidence that exercise can lead to various benefits in mental health and resilience is increasing [16,124-129]. This positive impact was achieved in supervised as well as unsupervised exercise programs. Here, we implement a study design that addresses the link between aerobic capacity and resilience from a multifactorial perspective to understand why some people are more resilient to stress than others. To follow this question, we will investigate the association between innate and trained aerobic capacities in the form of VO_2_peak of healthy, physically inactive adults and their resilience expressed primarily by salivary cortisol level changes and emotion regulation ability in response to different stress paradigms. We hypothesize that (1) participants with a high innate aerobic capacity will show a higher resilience to stress compared with participants with low aerobic capacity. Furthermore, we hypothesize that (2) 8 weeks of individually structured interval-type and continuous endurance exercise training remotely supervised by a web-based approach will improve the aerobic capacity of healthy inactive adults and that (3) the change from sedentary to an active lifestyle will improve resilience. In this study setting, we will be able to exploratively examine the molecular link between the effects of acute and chronic physical exercise and improved resilience to stress.

### Strengths and Limitations

The strengths of our web-based, supervised physical exercise training approach with a focus on increasing VO_2_peak in healthy, physically inactive adults are as follows: (1) participants are not location dependent for the training sessions; (2) individualized, gradual, and timely adjustment of training content based on the individual’s feedback reduces the risk of injury, avoids overtraining, and avoids ineffective training; and (3) only 1 sports therapist or trainer is needed for training management of several training groups or trainees, which obviously has economic advantages and reduces bias from different sports therapists. However, web-based training support also has disadvantages compared with presence (face-to-face) interventions. Notably, it requires access to the internet, which limits the study population. Furthermore, we are dependent on the correct and complete documentation of the training sessions by the participants. For an objective way to control reports on the training and to remotely supervise the participants in the IG, we included a smartwatch (Polar M430) that records the heart rate and distance of the individual training sessions. These are given to both the IG and CG participants to exclude an effect on the study outcome only by wearing the smartwatch. Furthermore, group or partner training can bring motivational and social benefits [130-132], which is not directly provided in our web-based physical exercise training support. This may reduce adherence of the participants to the study and, additionally, exclude the social aspect of the effect of an active lifestyle on resilience. Therefore, communication via the web-based platform is intended to be frequent and without any restraints toward the trainer. Finally, inexperience, fear, and the risk of injury can occur during an unaccustomed and intensive training load, which could be reduced or not arise at all through presence support. To counteract this, we have implemented a 2-week adaptation phase in our training intervention that will offer an easy training start and reduce the indicated risks. In addition, we address the individual needs of the participants based on their weekly feedback, so overload is unlikely to occur during the intervention. Adhering to the described improvements in web-based physical exercise interventions will offer the most individual and effective training support with a simultaneously reduced workload for the coach. With this, our research group has already successfully conducted similar studies using the internet for training interventions in patients with Barrett carcinoma, nonalcoholic fatty liver disease, depression, cystic fibrosis, and systemic lupus erythematosus [40-45].

Here, we selected an exercise intervention period of 8 weeks using a combination of interval-type training and continuous endurance exercise to efficiently enhance aerobic capacity in a short period. Interval training improves VO_2_peak more strongly in comparison with continuous exercise training [8]. Moreover, psychological benefits in attention, complex attention, and executive function were shown in high-intensity interval training compared with those in low-intensity training [133-135]. However, to counteract overtraining and risk of injury and to promote adherence, we complement interval-type training with endurance exercise sessions. A number of high-intensity interval training and moderate-intensity intervention studies with physically inactive participants decided for a comparable exercise intervention time leading to significant increases in VO_2_peak of 3%-19% [9-11]. Although a longer intervention period generally leads to higher increases in maximal oxygen uptake [122], it has been reported that enjoyment of interval training decreases with time [10]. Therefore, we considered a study design that used mixed model exercise sessions with a short intervention time of 8 weeks as efficient to enhance aerobic capacity in physically inactive adults and as suitable to analyze the impact on resilience.

Repeated stress induction and the estimation of resilience factors in a test-retest setting, as chosen in our study, are obstacles to resilience research. It was shown that for psychological stress tests, a test-retest design could lead to a learning effect, resulting in lower stress response [136,137]. Here, we use 2 different stress tests for T0 and T2 to reduce habituation to the applied stressor. By randomly assigning participants to the 2 groups, we intend to obtain the best estimate of the intervention effect on stress responses. However, differences in stress parameters at T2 might not exclusively be attributed to the intervention, as possible placebo effects (ie, simply receiving an intervention) or mediators may need to be considered. Previous studies analyzed similar between-subject comparisons, with less stress reactivity during the Trier Social Stress Test in trained men compared with untrained men [138]. In addition, we account for preintervention differences in stress reactivity and recovery by applying the SECPT at T0. However, as measures from both stress tests are not directly comparable, the experimental design does not permit within-subject analyses. To assess differences in individual changes within the IG, future studies may construct and apply parallel versions of a stress test pre and postintervention.

Several psychological interventions have been similarly used to increase resilience [139], and it might have been interesting to have a sport exercise group; a psychological exercise group that uses a psychoeducational element, such as cognitive restructuring; a mixed model group (sport and psychological); and a CG to obtain the influence of different types of interventions and their combinations on resilience to stress exposure. In our study, we focus on the physiological aspects of increasing VO_2_peak and its effect on resilience only. However, the identified relationships between molecular markers and exercise-induced resilience parameters in our setting may be further elucidated in mixed model interventions in follow-up studies.

We cannot exclude a selection bias so that persons who are generally interested in (1) psychological questions, (2) physical exercise, or (3) web-based services are rather addressed by the study announcement. Furthermore, because of a high time commitment for presence tests (2 measurement time points before and after the intervention), (4) people who live close to the survey site are more likely to participate and complete the study. On the basis of the World Health Organization guidelines on physical activity and sedentary behavior, we included individuals who were physically active for <150 minutes/week [140]. These individuals are described as insufficiently active, although this definition is very strict. Possibly, a cutoff point of physical activity <90 minutes/week would obtain a greater effect on the primary outcomes. Here, we decided in favor of the adherence to the study considering the training times that had to be completed.

Resilience is a dynamic and variable state that can be represented in a multifactorial manner. So far, individual instruments have failed to fully capture the variance of resilience [17,141,142]. For this reason, our study uses a wide variety of methods (physiological [blood markers, saliva markers, and hair] and psychological [questionnaires, stress tests, and emotion regulation]) to have a large number of independent predictors to clarify the variance in resilience to the greatest degree of accuracy. Owing to the high number of methods and the collected variables, spurious correlations or pseudoassociations may occur [143], especially when exploratory analysis is performed beyond hypothesis testing. The validity of these findings may be estimated in future studies.

### Conclusions

This study will allow us to investigate whether an increase in physical activity with a simultaneous improvement in aerobic capacity is associated with an increase in resilience and whether this effect is reflected in circulating molecular marker levels. These findings will help to reveal novel characteristics of human resilience and may offer novel approaches for the prevention and therapy of mental disorders by exercise prescription.

